### Inclusion and exclusion criteria

For the present study, women who are at least 5 years postmenopausal (based on the natural cessation of menstruation), aged 55–75 years with no major illness, and body mass index (BMI) between 25 and 35 kg/m^2^ will be included in the study.

Patients will be excluded if (1) they have a formal diagnosis of OA or rheumatoid arthritis (RA); (2) have chronic liver or renal disease, diabetes mellitus, and atherosclerosis; (3) have a history of allergy to mussels or seafood; (4) history of joint injury or trauma; (5) smoke or have alcohol intake more than two units per day; (6) receiving supplements for joint health, multivitamins/mineral, or omega-3 regularly and unwilling to stop these 4 weeks before the beginning of the trial; (7) currently being on hormone replacement therapy or less than 6 months prior beginning the trial; and (8) continuously taking anti-inflammatory drugs or glucocorticoids or NSAIDs on a daily basis.

### Enrollment and washout period, randomization

Eligible participants will be asked to stop consumption of oily fish (salmon, sardines, pilchards, tuna, etc.), and mussels 4 weeks before the beginning of the trial until the end of the trial (from weeks - 4, to week 12). After 4 weeks of washout, a randomization list will be generated by Excel and maintained by the main investigator. Participants will be randomized based on a double-blind randomization schedule and stratified randomization will be used to match participants based on BMI (overweight: 25–29.9 kg/m^2^ and obese: 30–35 kg/m^2^) and age (55–64, 65–75 years) distribution and allocated into two groups: whole meat GSM powder (*n* = 25) and placebo groups (*n* = 25) and will be followed up for 12 weeks. The participants and researchers will be blinded to the group allocation. Table 1 shows the schedule of enrollment, interventions, and assessments.

**Table 1 Tab1:** The schedule for enrollment, the interventions, and the assessments

	Study period				
	Enrollment	Allocation	Post-allocation		
Timepoint	*-t*_*2*_	*-t*_*1*_	*T*_*0*_	*T*_*6*_	*T*_*12*_
Enrollment:					
Eligibility screen	X				
Informed consent	X				
Allocation		X			
Washout period		X			
Intervention:					
Administration of GSM supplement and placebo			X	X	X
Assessments:					
Blood and urine sample collection			X	X	X
Pain assessment; VAS and KOOS			X		X
Body composition, DXA scan			X		X
Food intake; 3-day food record				X	
Compliance				X	X

### Procedure

After screening for eligibility, the informed consent form will be obtained and both groups will be invited to the Human Nutrition Research Unit at Massey University, Palmerston North three times: at baseline, week 6, and after 12 weeks. Subjects will be interviewed regarding their socio-demographic, dietary intake, and physical activity at baseline. At each visit, fasting blood and urine samples will be collected. A venous blood sample (20 ml) will be drawn after a 12-h overnight fast by a trained phlebotomist. Then blood samples will be centrifuged to obtain the serum and plasma EDTA and will be stored at − 80 °C until further biochemical analyses. All the ethical aspects pertaining to the storage of these samples have been approved by the Ethics Committee at Massey University. Body composition measurements including fat mass, lean mass, and fat percentage will be measured and analyzed using the Hologic Horizon A, Dual-energy X-ray Absorptiometry (DXA) at baseline and week 12.

Serum cartilage biomarkers CTX-II, COMP, and CPII will be assessed using commercially available sandwich enzyme immunoassay kits (BioVendor Research and Diagnostic Products, Karasek, Czech Republic). Bone marker CTX-I will be analyzed by electrochemiluminescence immunoassay using the Roche COBAS® e411 system (Roche Diagnostics, Indianapolis, IN, USA).

Urinary CTX-II will be measured using enzyme immunoassay (IDS immunodiagnostic System, Fountain Hills, Arizona, USA). Cytokine concentrations will be analyzed using BioLegend® LEGENDplex™ Multi-Analyte Flow Assay, following the manufacturer’s instructions. To determine vitamin D status at the baseline, calcidiol (25-hydroxyvitamin D [25(OH) D]) will be analyzed using isotope-dilution liquid chromatography-tandem mass spectrometry (ID-LC-MSMS).

The assays will be performed at accredited Clinical Laboratories and each specific biochemical assay analyzed will be done by the same person using the same equipment to mitigate the possible bias. We are planning to analyze vitamin D status at Canterbury Health, Christchurch, New Zealand. Serum iron, soluble transferrin receptors, transferrin, and ferritin will be measured to assess the iron status by measured at MedLab Central Palmerston North, New Zealand to provide information on iron status. Urine creatinine will also be assessed by the colorimetric method at Human Nutrition Research Unit at Massey University, Palmerston North, New Zealand. Creatinine will be used to correct the level of urinary CTX-II according to the urinary concentration.

### Intervention

Spray-dried GSM powder will be produced by Sanford Ltd (ENZAQ facility, Blenheim, New Zealand) using standard manufacturing processes. The proximate composition and microbiological load will be assessed by a commercial testing laboratory (Food Testing Laboratory of Cawthron Analytical Services; Nelson, New Zealand). The Association of Official Analytical Chemists (AOAC) methods for crude protein (AOAC 981.10), total fat (AOAC 948.15), moisture at 105 °C (AOAC 950.46) and ash (AOAC 920.153) will be used and carbohydrate content will be determined by calculation (100% − % crude protein − % total fat − % moisture − % ash). An aliquot of the total lipid extract from the GSM powder will be analyzed by gas chromatography mass spectrometry (GC-MS) according to AOAC 963.22. The placebo (sunflower seed protein powder) capsules will be purchased by Sanford Ltd from a commercial supplier. Both GSM and placebo will be encapsulated in gelatin capsules by a commercial facility (Alaron, Nelson NZ) and stored under nitrogen in the dark until use. Each capsule will contain 0.5 g of whole meat GSM powder or sunflower seed protein powder. The sunflower seed protein was selected as a placebo to provide a neutral protein source and to mimic GSM powder macronutrient composition and be as inert and non-bioactive as possible. The capsules will be completely similar in shape, size, and color (which will be dark to hide contents). Participants will receive three bottles of GSM supplement or placebo (each bottle contains 120 capsules) for 6 weeks distributed by a research at baseline. At the follow-up visit, the subjects will return their empty bottles and unused capsules to the researcher, to be counted and recorded and receive two new bottles along with their unused supplement. Participants will be required to consume 6 capsules (3 grams total) per day with meals. To allow the concealment and ability for a blinded trial, activated carbon sachets for absorbing moisture and odor in a bottle of supplement and placebo will be used; thus GSM capsule was indistinguishable from the sunflower seed protein powder used in the control group. At end of the study, the researcher and participants will be unblinded to the group allocation.

### Compliance

To assess subject’s compliance during the 12 weeks, diaries will be provided at the randomization to record the compliance to dietary and medication/supplement restriction. At weeks 6 and 12, subjects will return their unused capsules to the researcher to assess the rate of compliance. At weeks 6 and 12 consumption record diaries will be cross-checked with subjects. At the baseline and week 12, the plasma and erythrocyte membrane fatty acids will also be measured as an indicator to assess the adherence to study protocol. Participants in this trial are allowed to continue taking analgesic medications (panadol or paracetamol) as required.

### Safety

Minor gastrointestinal disturbances are expected as adverse effects based upon published literature. Information on all adverse events will be systematically collected in diaries provided by recording the history of any illness since the last visit and assessment of signs of concern at follow-up visit. Routine laboratory measurements including liver and kidney function tests, blood glucose (non-fasting), and lipid profile (triglyceride, total cholesterol, HDL-cholesterol, LDL-cholesterol) will be performed at the time of enrollment and after 12 weeks of treatment at MedLab Central Palmerston North, New Zealand by the certified phlebotomist. In case of any side effects or blood abnormalities, the person will be withdrawn and referred to their general practitioner for further examination. In case the experimental supplement is proven to be efficacious, the trial participants will be provided with a supplement post-trial.

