### Sample size

The sample size calculation applies to CTX-II/creatinine, CTX-II/procollagen II C-propeptide (PIICP) also referred as (CPII) CPII ratio, and cartilage oligomeric matrix protein (COMP) as the primary outcome variables. For CTX-II/ creatinine as well as CTX-II/ CPII a sample size of 24 is required to detect a 20% relative difference from baseline with 80% power. Hence, 25 subjects will be recruited for each group (GSM and placebo). For COMP as well as CPII a sample size of 7 is required to detect a 20% difference from baseline. This randomized double-blind placebo-controlled trial in parallel design recruit 55 (allowing for 10% potential dropout rate, with 27–28 sample in each arm).

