### Monitoring and quality assurance

The quality assurance of data will be checked by a trial supervisor. [name] is working with a researcher for monitoring the general trial processes, completeness, and accuracy of the protocol. The trial supervisor will have access to the results of data analysis, and progress report and any adverse event will be shared with the main supervisor on a weekly basis in the form of meeting.

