### Study outcomes

#### Primary outcomes

The difference in the mean of cartilage turnover markers (CPII, COMP, CTX-II) and bone resorption marker (CTX-I), measured at the end of the study in comparison with the week 6 and baseline values.

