### Statistical analysis

Statistical analysis will be performed using IBM statistics software version 25 (Armonk, NY, USA). The values of variables will be presented as mean ± standard deviation. Normality tests will be assessed through Shapiro-Wilk tests carried out on each parameter before analysis. Analysis includes all the participants (intent to treat) determining the baseline characteristic. Additional analysis will be performed per protocol on participants with 80% or higher adherence to study protocol. Two-way repeated measures ANOVA will be used to determine differences within groups (pre vs. post) as a repeated factor and intervention (GSM vs. placebo) as a fixed factor, with the model adjusted for the BMI and age, physical activity, and baseline vitamin D status. Post hoc analysis with Bonferroni adjustments will be performed for multiple comparisons. Statistical significance will be set at a level of 0.05.

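### The safety rule withdraws the person for any side effect although minor ones are expected, so read literally it can cost primary biomarker samples

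*Protocol article*

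**What the plan says.** All references are to the protocol article.

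- **Safety** predicts mild events: "Minor gastrointestinal disturbances are expected as adverse effects based upon published literature". All adverse events are gathered through diaries, by "recording the history of any illness since the last visit and assessment of signs of concern at follow-up visit". The consequence of an event is then fixed: "In case of any side effects or blood abnormalities, the person will be withdrawn and referred to their general practitioner for further examination". Routine safety bloods "will be performed at the time of enrollment and after 12 weeks of treatment".
- **Monitoring and quality assurance** adds that "any adverse event will be shared with the main supervisor on a weekly basis in the form of meeting".
- **Primary outcomes** defines the cartilage and bone markers as "measured at the end of the study in comparison with the week 6 and baseline values". Under **Procedure**, blood and urine are taken at each of three visits: baseline, week 6 and week 12.
- **Statistical analysis** names the population: "Analysis includes all the participants (intent to treat) determining the baseline characteristic".
- **Sample size** states that "a sample size of 24 is required to detect a 20% relative difference from baseline with 80% power", sets 25 women per group, and raises recruitment to 55 for 10% dropout.

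**The concern.** The same section forecasts a minor event and makes any such event a ground for removal. The rule has no threshold of severity, seriousness or relatedness. It acts on the person, and the article does not say that she is still sampled afterwards.

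If it is followed as written, primary data are lost because of something that happens after randomisation and that the capsules may cause. The values of these women must then be left out or imputed, whichever analysis method is chosen. The primary comparison would lean toward women who tolerate the capsules, and the loss would draw on the same small reserve that has to cover ordinary dropout.

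This is a risk, not a demonstrated bias. The article reports neither a side-effect rate nor a difference between arms.

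**Working it through.** **1. What can be lost, and when**

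| When the event surfaces | Samples at risk under the literal rule |
|---|---|
| Reported before week 6 | week 6 and week 12 |
| At the week 6 visit, or between weeks 6 and 12 | week 12 (a week 6 value can remain) |
| At the week 12 visit | possibly none (coincides with the final sample) |

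Laboratory abnormalities add little, because the safety bloods are scheduled only at enrollment and after 12 weeks.

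**2. The plan's own figure**

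50 × 1.10 = 55, so the recruitment target reproduces. The alternative 50 / 0.90 = 55.6 rounds up to 56, which is within one. The required 24 cannot be checked independently because no standard deviation is given. I read it as per arm, since 25 per group follows from it.

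**3. The reserve**

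- Against 24 per arm: 55 − 2 × 24 = 7 women (12.7% of 55).
- Against the target of 50: 55 − 50 = 5 women.

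**4. Chance of exceeding the reserve**

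The number of women lost is taken as Binomial(55, p). Every p is an assumption.

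| Outcome loss p | Expected losses (55p) | P(more than 7) | P(more than 5) |
|---|---|---|---|
| 5% | 2.75 | 0.6% | 6% |
| 10% | 5.5 | 18% | 48% |
| 15% | 8.25 | 60% | 85% |
| 20% | 11 | 88% | 98% |

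Now suppose that half of the events surface only at week 12, with the final sample taken (also an assumption). Side-effect rates of 5%, 10%, 15% and 20% then mean losses of 2.5%, 5%, 7.5% and 10%. P(more than 7) becomes under 0.1%, 0.6%, 5% and 18%. P(more than 5) becomes 0.3%, 6%, 23% and 48%.

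**5. Power**

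I assume a two-sided two-sample t test at alpha 0.05. Setting power to 80% at 24 per arm gives a standardised difference d = 0.826. Power is then recomputed at n = 27.5 × (1 − loss) per arm, with equal loss in both arms.

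| Total loss | n per arm | Power |
|---|---|---|
| 0% | 27.5 | 85% |
| 5% | 26.1 | 83% |
| 10% | 24.8 | 81% |
| 15% | 23.4 | 79% |
| 20% | 22.0 | 76% |

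If the planned 10% ordinary dropout also occurs, total loss = 1 − 0.9 × (1 − p), where p is now the side-effect withdrawal rate.

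| Side-effect withdrawal p | Total loss | Power |
|---|---|---|
| 0% | 10% | 81% |
| 5% | 14.5% | 79% |
| 10% | 19% | 77% |
| 20% | 28% | 72% |

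**6. Bias**

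Let p₁ and p₂ be the losses in the two arms, and D₁ and D₂ the differences, in SD, between women lost and women who stay. The shift in an observed-only contrast is p₁D₁ − p₂D₂. With D₁ = D₂ = 0.5 SD (assumed):

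- Losses of 10% and 5%: 0.10 × 0.5 − 0.05 × 0.5 = 0.025 SD, and 0.025 / 0.826 = 3% of d.
- Losses of 20% and 10%: 0.20 × 0.5 − 0.10 × 0.5 = 0.05 SD, or 6% of d.
- Equal losses and equal differences: 0.

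**The case against.** **The wording may be looser than the intent.** Withdrawal is paired with referral to a general practitioner, which suggests events that need medical work-up, not every mild stomach upset. It could also mean stopping capsules only, in which case no sample is lost. Both readings are possible. But the sentence covers any side effect and names the person, so staff who keep a woman with mild nausea in the study depart from the text by individual judgement. A clarification is needed on either reading.

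**This is a condensed article.** Definitions, thresholds and post-withdrawal sampling could sit in the full protocol, and their absence alone would be no finding. The problem is the rule that is stated. No analysis plan can recover samples that were never taken.

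**The route to early loss is thin.** The weekly meeting passes events to the supervisor; it is not weekly collection from participants. The only scheduled visits after baseline are at weeks 6 and 12, when samples are due anyway. This stands in large part: the more plausible loss is the week 12 sample alone, and losing both needs a report before week 6.

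**The numbers rest on assumptions and the effect is modest.** This also stands. The reserve is not a cliff: about 47 evaluable women (23.5 per arm) still give 79% power. A near-even chance of exceeding a reserve of 5 at 10% loss follows for any sample inflated to match its expected dropout. The effect size is back-solved from a two-sample reading, while the article speaks of a difference from baseline.

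**Little can still change.** Trial status reports recruitment complete, with data collection expected to finish in September 2021. This limits the benefit but does not remove it.

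**Conclusion.** The concern holds in conditional form. As written, the rule turns an expected minor effect into grounds for ending a woman's participation, puts mainly the week 12 primary samples at risk, and pulls against the intent-to-treat aim.

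Its size cannot be derived from the article. Across the assumed range it is moderate: a few points of power on its own, and power below the planned 80% once side-effect withdrawals of 5% or more come on top of the planned dropout. In the illustrations of unequal loss, the bias is 3% to 6% of the design effect; it is zero if loss and its relation to the outcome match across arms. These figures depend on reading 24 as per arm, a two-sided two-sample test, and assumed loss rates and outcome differences.

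The change is one that should be made because the loss is avoidable and cheap to prevent. The point does not invalidate the design. Confidence is medium, chiefly because the meaning of withdrawal is open.

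**What to change.** Replace the sentence in Safety with a rule that:

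1. stops the capsules only for serious or intolerable events or clinically significant laboratory abnormalities, with the threshold set by the investigators and general practitioner referral kept;
2. states that women who stop capsules keep their scheduled week 6 and week 12 blood and urine sampling and other assessments unless they withdraw consent;
3. analyses them as randomised, using all observed visits, and reports discontinuations by arm and reason.

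If withdrawal was always meant as stopping capsules only, say so.

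The cost is a wording change and a few already planned visits attended off capsules. Keeping women who stopped early slightly dilutes the estimated effect. Samples already missed cannot be recovered, so the benefit is confined to women still in follow-up, the analysis and the reporting.

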### Monitoring and quality assurance

The quality assurance of data will be checked by a trial supervisor. [name] is working with a researcher for monitoring the general trial processes, completeness, and accuracy of the protocol. The trial supervisor will have access to the results of data analysis, and progress report and any adverse event will be shared with the main supervisor on a weekly basis in the form of meeting.

### Data collection and management

Participant confidentiality will be maintained through a unique ID system, and the participant identification information will not be exposed to anyone outside the trial team. All personal data will be destroyed at the end of the trial. Scientific data, filed on paper, will be shredded, and electronic data will be deleted from our computer records and databases after 10 years. For the first 5 years, it will be stored in a locked filing cupboard within a locked office. For the last 5 years, it will be stored in a secure archive where all data is stored in boxes labeled by barcode only. It is accessible by nominated staff only who require pin numbers for ID. The results of the trial will be disseminated in conference presentations, manuscripts for publication.

### Study outcomes

#### Primary outcomes

The difference in the mean of cartilage turnover markers (CPII, COMP, CTX-II) and bone resorption marker (CTX-I), measured at the end of the study in comparison with the week 6 and baseline values.

#### Secondary outcomes

The difference in the mean of inflammatory markers including hs-CRP and 13 cytokines namely IL-1β, interferon alpha-2 (IFN-α2), IFN-λ, TNF-α, monocyte chemoattractant protein-1 (MCP-1), IL-6, IL-8, IL-10, IL-12p70, IL-17A, IL-18, IL-23, and IL-33, as well as serum soluble transferrin receptor levels as an indicator of iron status measured at the end of the study in comparison with baseline values. Changes in body composition including fat mass (FM), lean mass (LM), and fat percentage, joint pain, and knee function will also be measured.

### Assessment of dietary intake

Dietary intake, a 3-day diet diary (3-DDD) over non-consecutive days (including one weekend day), will be collected one time during the study. At the first visit, an instruction on how to complete the food diary will be provided to the participants by the trained researcher. The 3-DDD will be used to collect information on participants’ food and beverage intake using household measurement tools to assist subjects in estimating the portion sizes of the food. Brand name of food products, recipes, and method of food preparation will be described. Dietary intake will be analyzed with Food works 9 professional, Xyris software.

### Assessment of physical activity

Physical activity will be assessed using the New Zealand Physical Activity Questionnaire-short form (NZPAQ-SF) [19]. The NZPAQ has previously been validated by Boon et al. Physical activity will be measured by METs-min/day which is computed by using the scoring protocol of IPAQ for continuous score [20]. MET values and formula for calculation of MET-minutes will be assessed and used as below:
Walking MET-minutes/week at work = 3.3 × walking minutes × walking days at workModerate MET-minutes/week at work = 4.0 × moderate-intensity activity minutes × moderate intensity days at work.Vigorous MET-minutes/week at work = 8.0 × vigorous-intensity activity minutes × vigorousTotal Work MET-minutes/week = sum of walking + moderate + vigorous MET-minutes/week scores at work

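### The printed physical-activity score counts only activity at work, and its weekly unit conflicts with the per-day unit announced, so the named covariate would not measure total activity

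*Protocol article*

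**What the plan says.** All references are to the Protocol article.

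- **Instrument and timing.** "Physical activity will be assessed using the New Zealand Physical Activity Questionnaire-short form (NZPAQ-SF"). Under Procedure: "Subjects will be interviewed regarding their socio-demographic, dietary intake, and physical activity at baseline".
- **Announced measure.** Assessment of physical activity: "Physical activity will be measured by METs-min/day which is computed by using the scoring protocol of IPAQ for continuous score".
- **Status of the formulas.** They are introduced with "MET values and formula for calculation of MET-minutes will be assessed and used as below", so they are the rule and not an example.
- **Content of the formulas.** The walking, moderate and vigorous scores are each labelled as weekly and as at work. The moderate line, for instance, is "4.0 × moderate-intensity activity minutes × moderate intensity days at work". The last line defines a work total as the "sum of walking + moderate + vigorous MET-minutes/week scores at work". There is no term for leisure, home or transport, no overall total and no conversion to a day.
- **Use.** Statistical analysis specifies a two-way repeated-measures ANOVA "with the model adjusted for the BMI and age, physical activity, and baseline vitamin D status". It does not say which activity score is meant.

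**The concern.** The eligibility criteria set an age range of 55-75 years and say nothing about employment, so some participants may do no paid work. On the printed rule their score is fixed at zero, and the variable would partly separate women who are active at work from the rest instead of ranking them by how active they are.

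Two uses are affected. The covariate in the main model would be a poor stand-in for what its name says. The descriptive activity figures would understate total activity, and they could also carry the wrong unit, since "Physical activity will be measured by METs-min/day" stands beside formulas that give weekly values.

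**Working it through.** The plan states no figure for this variable that could be reproduced, so the check applies the printed formulas and then asks what reaches the treatment comparison.

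**Inputs from the article.** Weights of 3.3 (walking), 4.0 (moderate) and 8.0 (vigorous), each multiplied by minutes and days at work, then summed. The vigorous line stops before its days term; it is read here as days, in parallel with the other two. The activity patterns below are assumed for illustration.

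**1. No activity at work.** 3.3 × 0 + 4.0 × 0 + 8.0 × 0 = 0, whatever is done outside work.

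**2. Ranking.**
- A woman not in work who walks 60 min on 7 days: all-activity total 3.3 × 60 × 7 = 1386 MET-minutes/week; printed score 0.
- A woman who walks 10 min on 5 days at work and does nothing else: printed score 3.3 × 10 × 5 = 165.
- The printed score ranks the second woman as the more active.

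**3. Unit.** Take 30 min walking on 5 days and 30 min moderate activity on 2 days, all outside work. An all-activity total is 3.3 × 30 × 5 + 4.0 × 30 × 2 = 495 + 240 = 735 MET-minutes/week, or 735 / 7 = 105 per day. A weekly value reported as a daily one would be 7 times too high.

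**4. Does the unit matter to the model?** In one simulated data set of 25 per arm, a linear model was fitted with the work score per week and again with it divided by 7. The treatment estimate (0.9066), its SE (0.2786) and p (0.0021) were the same in both. Only the covariate's own coefficient changed, from 0.000351 to 0.002454, a factor of 7.

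**5. Does work-only scoring matter to the model?** 2,000 simulated trials of 25 per arm were run for each assumed share of women in work. Assumptions: gamma-distributed activity (shape 1.5; scale 500 at work for those employed, 700 elsewhere for all), a single outcome falling by 0.0005 per unit of total activity, residual SD 1, true treatment effect 0.5.

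| Share in work | Correlation of work score with total | SE of effect, no covariate | SE, work score | SE, total score |
|---|---|---|---|---|
| 20% | 0.41 | 0.315 | 0.313 | 0.284 |
| 50% | 0.55 | 0.322 | 0.313 | 0.289 |
| 80% | 0.58 | 0.321 | 0.313 | 0.288 |

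The mean treatment estimate was 0.48 to 0.50 with either covariate, so there is no bias. Under these assumptions the work score recovers little of the precision that the total score gives. A second set of assumed distributions, with 30-60% in work, gave correlations of 0.59 to 0.69. That range does not overlap with 0.41 to 0.58, which shows that the size depends on the inputs chosen.

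**The case against.** The strongest reply is that the article may have printed one block of a longer scoring scheme. The last line is labelled as a work total, which reads like a subtotal for one domain. The section also points to an external scoring protocol, and Statistical analysis speaks only of physical activity without naming the work total. A reader might infer that the model certainly adjusts for work activity. The article does not establish that: the link is an inference. It is a reasonable one, because these formulas are presented as those to be used and no other computed score is given.

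Other stronger readings also fail:

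- **That the unit conflict distorts the analysis.** It cannot. Rescaling a covariate by 7 leaves the treatment estimate, SE and p unchanged. The formulas themselves are labelled weekly, so a 7-fold error arises only if a weekly value is reported as a daily one.
- **That a definite share of precision is lost.** The article gives no employment rate, no activity distribution and no relation between activity and the biomarkers. The simulations also use a single outcome. In the planned pre-post by group comparison, a stable effect of baseline activity on marker level cancels within each woman, so the covariate helps only as far as activity predicts change.
- **That the treatment comparison is biased.** It is not: activity is recorded at baseline and allocation is randomised.
- **That the vigorous formula is wrong.** Its missing days term may be a loss in text extraction, since the line breaks between formulas are also lost, and the parallel lines make the intended term clear.

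What remains is that the text fixes a scoring rule that does not fit the construct it names.

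**Conclusion.** The point holds in limited form. As printed, the rule scores only activity at work, gives a woman with none a score of 0, and conflicts with the announced daily unit. The physical-activity covariate and the reported activity values would then not measure total activity. This is an explicit rule that is badly fixed, not detail left to a fuller document.

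The consequence is moderate. The randomised comparison stays unbiased. There may be some loss of precision, of unknown size and possibly negligible for the change comparison, and a baseline variable would be mis-described. The conclusion assumes that the printed formulas are applied literally and that the covariate is the score they define. How many women are affected depends on how many have no activity at work, which the article does not say.

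**What to change.** 1. In Assessment of physical activity, define one total MET-minutes score over all walking, moderate and vigorous activity that the questionnaire records, without the restriction to work.
2. Use one unit throughout: either MET-minutes/week, or that total divided by 7 and labelled per day.
3. Check the vigorous formula against the source file and complete it with its days term if this is missing there.
4. In Statistical analysis, name that total, with its unit, as the physical-activity covariate.
5. If the questionnaire recorded only work activity, label the variable as work activity and do not present it as adjustment for total physical activity.

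The cost is small: a change of wording and rescoring of a baseline questionnaire. Trial status says that recruitment is complete and data collection still open, so the definition can be fixed before analysis, which also avoids a choice of covariate definition after the data are seen.
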